### Handling missing data & population analysis

4.10

Primary analysis: Intention-to-treat (ITT).Missing data management: Multiple imputation will be used if missing exceeds 10% and a per-protocol analysis will be done alongside ITT analysis to assess robustness.

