### Withdrawal criteria

3.8

Participants may be withdrawn from the study under the following circumstances:

Occurrence of a serious adverse event requiring urgent medical intervention.Initiation of pharmacological treatment for insomnia during the study period.Emergence of a psychiatric condition requiring immediate clinical management.Voluntary withdrawal of consent.

Symptom fluctuation or worsening insomnia severity alone will not constitute automatic withdrawal. Participants experiencing worsening symptoms will undergo clinical evaluation and supportive management. Non-compliance with the intervention schedule will be documented but will not automatically result in withdrawal. All randomized participants will be included in the intention-to-treat analysis wherever feasible.

Withdrawal decisions due to safety concerns will be made by the Principal Investigator in consultation with the Co-Investigator and documented in the CRF.

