### Exploratory primary outcome

4.1

(Assessed at Week 4—end of intervention phase).

Insomnia Severity Index (ISI) — change from baseline to Week 4.

Measurement variable: ISI total score (range 0–28).Analysis metric: Mean change from baseline to Week 4; between-group mean difference with 95% confidence interval.

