### Sample size

4.5

This study is designed as an exploratory randomized controlled trial intended to estimate preliminary between-group differences and assess feasibility parameters rather than to establish confirmatory superiority.

The sample size was estimated using the standard formula for comparison of two independent means:

$$n=\frac{2s_{p}^{2}{\left(Z_{1-\alpha /2}+Z_{1-\beta }\right)}^{2}}{{\left(\mu_{1}\mu_{2}\right)}^{2}}$$

where 
$s_{p}$
 represents the pooled standard deviation, 
$\mu_{1}-\mu_{2}$
 represents the expected mean difference between groups, 
$Z_{1-\alpha /2}$
, 
$Z_{1-\beta }$
 correspond to conventional planning parameters.

The expected post-intervention ISI mean in the intervention group (6.9) was informed by pilot observations in perimenopausal women receiving *Siro-pichu* and *Padabhyanga* with *Ksirabala Taila*. The expected post-intervention ISI mean in the control group (10.9) was derived from Ayabe et al. (49), a multicenter randomized controlled trial evaluating CBT-I in adults with pharmacotherapy-resistant insomnia. Although the Ayabe et al. study included both sexes, the majority of participants were women with a mean age of 52 years, supporting its relevance to the present perimenopausal population (49, 50). The anticipated mean difference between groups was therefore approximately 4 points on the ISI scale. A pooled standard deviation of 4.3 was derived from pilot data. Using a two-sided alpha of 0.05 and 90% power as conservative planning parameters with a 1:1 allocation ratio, the required sample size was estimated at approximately 26 participants per group. Allowing for an anticipated attrition rate of 15%, the final planned sample size was set at 31 participants per arm (total *N* = 62). This calculation was applied as a pragmatic planning tool to avoid underestimation of participant numbers and to permit preliminary effect-size estimation. The study is not powered for confirmatory hypothesis testing, and findings will be interpreted within an exploratory, hypothesis-generating.

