#### Retention

4.8.4

Participation in this study is entirely voluntary. Participants may withdraw at any time without penalty or loss of entitled care and this will be documented in study records. Participants who withdraw will not undergo any additional data collection or follow-up assessments. Data collected prior to withdrawal will be retained for analysis unless the participant explicitly requests removal, subject to regulatory and ethical guidelines. Efforts will be undertaken, where appropriate and ethically permissible, to minimize unnecessary dropouts while respecting participant autonomy. All study records will be retained for a minimum of 5 years following study completion in accordance with institutional policy and Indian Council of Medical Research (ICMR) guidelines.

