#### Exploratory primary outcome analysis (week 4)

4.9.1

Change from baseline to Week 4 in ISI score will be summarized for each group. Between-group differences in mean change will be estimated using Independent *t*-tests for normally distributed data or Mann–Whitney U tests for non-normally distributed data. Effect sizes with 95% confidence intervals will be reported. *p*-values will be presented for descriptive purposes and interpreted cautiously within the exploratory framework.

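### Multiple imputation starts only above 10% missing, on an unstated base; at or below that no method is given, and the ITT primary analysis by default leaves out women without a Week 4 ISI

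*Protocol article*

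**What the plan says.** - **Missing data (4.10).** The primary analysis is ITT, and "Multiple imputation will be used if missing exceeds 10" per cent. The base of the percentage is not given, nor is any method for 10% or less. The only robustness check named is a per-protocol analysis.
- **ITT population (3.8).** "All randomized participants will be included in the intention-to-treat analysis wherever feasible".
- **Primary endpoint (4.1).** "Mean change from baseline to Week 4; between-group mean difference with 95% confidence interval".
- **Primary method (4.9.1).** "Between-group differences in mean change will be estimated using Independent *t*-tests for normally distributed data", with Mann-Whitney as the alternative. Section 4.9.2 rules out formal repeated-measures or longitudinal modelling.
- **After withdrawal (4.8.4).** "Participants who withdraw will not undergo any additional data collection or follow-up assessments". One listed ground for withdrawal (3.8) is "Initiation of pharmacological treatment for insomnia during the study period".
- **Planned losses (4.5).** "Allowing for an anticipated attrition rate of 15" per cent, which takes the trial to 31 per arm, 62 in all.
- **Data available (Table 1 in 4.8.1).** ISI is scheduled at baseline, Week 2 and Week 4.

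**The concern.** The rule lets the observed amount of missing data decide how the primary result is computed. Above the threshold every randomised woman can contribute through imputation. At or below it, nothing in the article gives a score to a woman without a Week 4 ISI. A two-sample test on change cannot use her, and no planned model would draw on her Week 2 value. The result would be called ITT but would in practice be a complete-case result.

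This matters because missingness may be related to outcome: starting drug treatment for insomnia is a ground for withdrawal, and assessment then stops. The trial's stated product is a preliminary effect size to inform a later trial, so bias in that estimate would carry forward. The per-protocol analysis does not help. It varies the adherence requirement, not the assumption about missing scores, and women without a Week 4 ISI are absent from it too.

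**Working it through.** **Inputs from the article (4.5):** 31 per arm, N = 62, SD 4.3, planned difference 4 ISI points (6.9 versus 10.9), attrition 15%, two-sided alpha 0.05, power 90%.

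**1. The plan's own figure.** n = 2 × 4.3² × (1.960 + 1.282)² / 4² = 24.29. Adding the small-sample term 1.96²/4 = 0.96 gives 25.25, rounded up to 26 per group. Then 26 / 0.85 = 30.6, rounded up to 31. The sample size reproduces and is not affected by this point.

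**2. Where the rule switches.**
- Overall reading: 6/62 = 9.7%, not above 10%, so 62 − 6 = 56 women are analysed. 7/62 = 11.3%, so imputation runs and 62 are analysed.
- On that reading the rule does not see imbalance: six missing in one arm is 6/31 = 19.4% of that arm, and imputation is still not triggered.
- Per-arm reading: 3/31 = 9.7% is the limit in each arm and 4/31 = 12.9% triggers imputation, so six missing in one arm would be imputed.

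**3. How often the branch without imputation is reached (overall reading).** P(X ≤ 6) with X binomial, n = 62:

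| Missing rate at Week 4 | P(6 or fewer missing) |
|---|---|
| 5% | 0.97 |
| 8% | 0.78 |
| 10% | 0.57 |
| 15% (planned attrition) | 0.16 |

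At 15% the expected number missing is 0.15 × 62 = 9.3. The lower rates are assumptions; the article gives no Week 4 rate.

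**4. How six missing women would split if missingness were unrelated to arm.**
- All six in one arm: 2 × C(31,6) / C(62,6) = 0.024.
- 5 versus 1 or worse: 2 × [C(31,6) + 31 × C(31,5)] / C(62,6) = 0.20.

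**5. Size of the shift for an assumed gap.** SE of the difference = 4.3 × √(2/31) = 1.09. If the missing women's mean change is k points worse than that of the completers in their arm, leaving out six from one arm moves the difference by (6/31) × k:
- k = 2: 0.39 points (0.35 SE)
- k = 4: 0.77 points (0.71 SE)
- k = 6: 1.16 points (1.06 SE)

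A 5 versus 1 split at k = 4 gives (4/31) × 4 = 0.52 points (0.47 SE). No figure in the article supports any particular k.

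**6. Size under a dropout model.** Simulation of 4,000 trials, 31 per arm. Week 4 means (6.9 and 10.9) and SD (4.3) are from the article. All else is assumed: baseline mean 15 in both arms; Week 2 means 12 and 13; baseline and Week 2 SDs 3.3 and 4.0; correlations 0.5 (baseline and Week 2), 0.4 (baseline and Week 4) and 0.7 (Week 2 and Week 4); dropout weight exp(0.35 × Week 2 ISI). The selection is strong: one Week 2 SD multiplies the weight by exp(1.4), about 4.

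| Split of six missing | Complete-case bias, points | In SE |
|---|---|---|
| 6 v 0 | 0.30 | 0.27 |
| 5 v 1 | 0.22 | 0.20 |
| 4 v 2 | 0.11 | 0.10 |

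The bias favours the arm that loses more women. Imputation by arm from baseline and Week 2 ISI left about 0.01 points in each case. That near-zero figure follows from letting dropout depend on the observed Week 2 score; it would be larger if dropout depended on unobserved values.

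**The case against.** **The complete-case method is not written down.** True. It is what the stated tests do by default when no other rule applies, and the full SAP, which is not shown, may say more. The trigger itself is fixed in the article, however, and a SAP would have to override it to remove the switch.

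**The inclusion statement is qualified by feasibility.** Also true, so a reader should not infer a flat contradiction with ITT. The qualifier does not settle the matter: the plan itself treats imputation as feasible once the threshold is passed.

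**Planned attrition would trigger imputation anyway.** Largely right. The 15% inflates a calculation on post-intervention means, and if it applied at Week 4 imputation would run about 84% of the time. The article attaches no time point to the 15%, and follow-up continues to Week 16, so better retention at Week 4 is possible but not shown.

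**Stronger readings that the documents do not support.**
- A reader might infer that 19% of one arm could typically go unscored. That needs the overall reading of the threshold and a 6 versus 0 split, which has a 2.4% chance if missingness is unrelated to arm.
- A reader might infer that the home oil regimen gives the add-on arm an extra route out of the trial and so fixes the direction of bias. Section 3.8 says non-compliance does not automatically mean withdrawal, nor does worsening insomnia alone. Unblinded control women might leave more often instead.
- A reader might infer that the Mann-Whitney option cannot be combined with imputation. The index U/(n1 × n2) has a standard error and can be pooled; it is the test's p-value that has no direct Rubin pooling.

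**The trial is exploratory.** This lowers the severity. It does not remove the point, because effect-size estimation is what the trial is for.

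**Conclusion.** The point stands as a minor one. The article fixes a data-dependent imputation rule with no stated base and no method at or below the threshold, and on an overall reading one woman changes both the primary method and the analysed population. The gap matters mainly if Week 4 retention is better than the planned 15% loss. With six missing, the likely bias is about 0.1 to 0.3 ISI points, against a planned difference of 4. Larger shifts need extreme splits together with large assumed gaps. The direction is unknown. The conclusion rests on the complete-case default, the overall reading of the 10% and the simulation assumptions listed above. It does not show that the primary result will be materially wrong.

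**What to change.** In 4.10, delete the 10% trigger and state that any missing Week 4 ISI, whatever the amount, will be handled by multiple imputation within arm from baseline and Week 2 ISI. The between-group mean difference in change would be pooled by Rubin's rules, so that all randomised women contribute (apart from any whose data are removed at their own request under 4.8.4). Report the complete-case result as a sensitivity analysis. An analysis that worsens the imputed scores by a fixed amount is optional; it would test the missing-data assumption, which the per-protocol analysis does not.

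The cost is a sentence or two in 4.10 and a little more analysis work. No new visits, data or participants are needed, since baseline and Week 2 ISI are already scheduled. The interval may be slightly wider than the complete-case one. The change should be made before outcome data are seen.

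### The primary metric is a mean difference in ISI change, but the non-normal branch uses a Mann–Whitney U test, which does not estimate one and gives nothing directly poolable if multiple imputation is triggered

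*Protocol article*

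**What the plan says.** Four parts of the protocol article bear on this point.

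- **Section 4.1 (Exploratory primary outcome)** sets the analysis metric without any condition on the shape of the data: "Mean change from baseline to Week 4; between-group mean difference with 95% confidence interval".
- **Section 4.9.1 (Exploratory primary outcome analysis)** says the group difference in mean change is to be estimated with "Independent *t*-tests for normally distributed data or Mann–Whitney U tests for non-normally distributed data". It adds: "Effect sizes with 95% confidence intervals will be reported". It does not name the effect size for either branch.
- **Section 4.10 (Handling missing data)** makes intention-to-treat primary and states: "Multiple imputation will be used if missing exceeds 10" per cent.
- **Section 4.5 (Sample size)** plans for loss above that threshold: "Allowing for an anticipated attrition rate of 15%, the final planned sample size was set at 31 participants per arm". It does not say by which week the 15% is expected.

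Section 4.8.4 adds that nothing further is collected after a withdrawal, so a withdrawal before Week 4 leaves the primary outcome missing.

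**The concern.** The trial describes its purpose as preliminary effect-size estimation, so the estimate and its interval are its main product. In one of the two branches of 4.9.1, the named method does not produce the quantity that 4.1 promises. The analyst would then have to decide, after seeing the data, what to report as the primary estimate: a mean difference from some other method, a shift in location, or a probability that one group does better.

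Multiple imputation makes this harder. Its pooling step needs an estimate and a variance from each completed dataset, and the Mann–Whitney test as named supplies a rank statistic and a p-value.

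**Working it through.** **1. The plan's own sample size.** Inputs from 4.5: difference 10.9 − 6.9 = 4, SD 4.3, two-sided alpha 0.05, power 90%, attrition 15%.

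- Normal formula: 2 × 4.3² × (1.960 + 1.282)² / 4² = 24.29, so 25 per group. The t-distribution version gives 25.29, so 26.
- With attrition: 26 / (1 − 0.15) = 30.6, so 31 per arm and 62 in all.

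The plan's figures reproduce. They rest on a comparison of two means, which is the metric in 4.1.

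**2. What each branch of 4.9.1 yields.**

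| Branch | What the named test gives | Is it the 4.1 metric? |
|---|---|---|
| t-test | mean difference, standard error, 95% CI | yes |
| Mann–Whitney U | rank statistic U and a p-value; U/(n₁n₂) estimates P(X>Y) | no |

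Under normality with equal SDs, P(X>Y) = Φ(difference / (SD × √2)). With the plan's figures this is Φ(4 / (4.3 × 1.414)) = Φ(0.658) ≈ 0.74. It depends only on the ratio 4/4.3. Halving both numbers (2 points, SD 2.15) gives the same 0.74, so the rank quantity does not determine the difference in ISI points. A Hodges–Lehmann estimate is on the ISI scale, but it equals the mean difference only under added assumptions about shape.

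**3. What pooling needs.** For M imputed datasets with estimates Qₘ and variances Uₘ, Rubin's rules take the mean of the Qₘ as the estimate. The total variance is T = W + (1 + 1/M)B, where W is the mean of the Uₘ and B the variance of the Qₘ. A mean difference with its standard error fits this directly; a raw U or a p-value does not.

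**4. Whether a rank quantity could be pooled.** It could. In a simulation, logit P(X>Y) with its rank-based variance was pooled by Rubin's rules (31 per arm, 15% missing completely at random, M = 20, 1,500 trials per scenario). Baseline SD 3.5, slope 0.5 and normal data were assumed and are not in the documents. An estimate, interval and p-value came out every time. Rejection was 3.4% under no effect. Under a 4-point effect it was 88%, with a mean estimate of 0.74. The result is a probability, not a difference in ISI points.

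**5. How likely imputation is.** Above 10% of 62 (6.2) means at least 7 missing. Binomial P(X ≥ 7 of 62) by the true missing rate at Week 4:

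| Missing at Week 4 | P(threshold passed) |
|---|---|
| 15% | 84% |
| 12% | 63% |
| 10% | 43% |
| 8% | 23% |
| 5% | 3% |

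**6. How likely the Mann–Whitney branch is.** The article names no normality check, so this needs an assumption. With Shapiro–Wilk p < 0.05 in either arm, 5 missing per arm, and baseline–Week 4 correlations of 0.3 and 0.5, the observed data were flagged in 11.5% and 14.0% of 1,500 simulated trials each. Two tests at 5% flag 1 − 0.95² = 9.75% of trials even when the data are exactly normal, so most of these flags are false alarms. If the two conditions are independent and 15% are missing at Week 4, both hold in about 0.84 × 11.5% = 9.7% to 0.84 × 14.0% = 11.8% of trials. The true rate depends on the real shape of ISI change, which the documents do not give.

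**The case against.** The strongest reply has four parts.

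- **The mean difference is not lost.** Section 4.1 states it unconditionally, so it can be computed and pooled whichever test supplies the p-value, and 4.9.1 separately promises intervals. That reading is workable, but it is not what 4.9.1 says: that section names the tests as the means of estimating the difference in mean change. The two sections have to be reconciled, and the text does not say how.
- **Pooling detail belongs in the analysis plan.** Section 4.8.5 refers to a pre-specified plan and section 8 offers it on request; it is not shown. The missing combining rule is therefore no defect in itself, and this part stands. But a combining rule alone would not turn a Mann–Whitney result into the metric of 4.1.
- **The branch is uncommon.** A reader might infer from the 15% and 10% figures that the plan expects to end up with imputation and a Mann–Whitney test together. The documents do not support that. The 15% has no time point, and follow-up runs to Week 16, so part of the loss may fall after the primary endpoint. Non-normality is a separate condition, met in a minority of simulated trials.
- **Everything is exploratory, with descriptive p-values.** True, and it limits the consequence for inference. It does not help the estimate, which is what an exploratory trial of this kind is for.

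Two stronger inferences also fail. One is that a Mann–Whitney analysis is impossible to pool and leaves no primary result; step 4 shows that a rank quantity pools without difficulty. The other is that imputed datasets would call for different tests. That presumes a shape check in each imputed dataset, which the article never states; one check on the observed data is an equally natural reading.

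**Conclusion.** The point holds as an inconsistency between two stated rules. Section 4.1 promises a mean difference with a 95% CI, and the non-normal branch of 4.9.1 names a test that does not estimate one. This is so with or without missing data. Under multiple imputation, the same branch also lacks a directly poolable estimate with a standard error, and any rank-based substitute would be a different quantity.

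Imputation is likely but not certain: about 84% if 15% are missing at Week 4, and much less if losses come later. The combination with the Mann–Whitney branch arises in roughly 10% to 12% of trials under the assumptions in step 6. The sample size is unaffected. This should be corrected before analysis, because otherwise the primary estimate depends on a choice made after seeing the data.

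**What to change.** In 4.9.1, state that the primary estimate is always the difference between groups in mean ISI change from baseline to Week 4, with its standard error and 95% CI, from one fixed linear comparison used whatever the shape of the data. In 4.10, state that when multiple imputation is used, this comparison is fitted in every imputed dataset and pooled by Rubin's rules with small-sample degrees of freedom. Keep the Mann–Whitney test as a supplementary analysis of observed data, labelled as addressing a different quantity.

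The cost is a sentence in each section. No new data, visits or participants are needed, and the sample size calculation, already based on two means, stays as it is.

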#### Adherence to Ayurvedic regimen

3.9.1

Adherence to *Siro-pichu* and *Padabhyanga* will be defined as completion of at least 80% of the prescribed applications during the intervention phase.Completion will be recorded in the Daily Sleep and Treatment Engagement Diary and reviewed during weekly follow-ups.Random tele-supervision (10% of participants) will be conducted to support procedural fidelity.

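### The per-protocol analysis named to assess robustness cannot test what is assumed about missing Week 4 ISI scores

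*Protocol article*

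**What the plan says.** Section 4.10 makes ITT the primary analysis. Under the missing-data item it then states two things: "Multiple imputation will be used if missing exceeds 10" per cent, and "a per-protocol analysis will be done alongside ITT analysis to assess robustness". No other analysis in the article is given the task of checking robustness.

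The other relevant text is spread over several sections:

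- **Section 3.8 (Withdrawal criteria).** Women may be withdrawn on "Initiation of pharmacological treatment for insomnia during the study period". The same section says "Symptom fluctuation or worsening insomnia severity alone will not constitute automatic withdrawal", and that "All randomized participants will be included in the intention-to-treat analysis wherever feasible".
- **Section 3.10.3.** Significant worsening of insomnia leads to a pause of the intervention and referral to a sleep specialist or psychiatrist.
- **Section 4.8.4 (Retention).** "Participants who withdraw will not undergo any additional data collection or follow-up assessments".
- **Section 4.5 (Sample size).** Attrition of 15% is expected, with 31 women per arm.
- **Sections 3.9.1 and 3.9.2.** Adherence to the oil procedures means "completion of at least 80% of the prescribed applications during the intervention phase"; adherence to CBT-I means at least six sessions.

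**The concern.** The Week 4 comparison depends on an assumption about women who have no Week 4 ISI. A robustness check for missing data has to change that assumption and show what happens to the estimate. A per-protocol analysis changes something else: it restricts the comparison to women who followed the protocol. A woman who withdrew before Week 4 is either left out of it or would have to be imputed on the same assumption as in the ITT analysis.

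This matters because the protocol's own rules contain a path from poor outcome to missing data: worsening, referral, insomnia medication, withdrawal, no further assessment. Each step is possible rather than certain. If the path is used more in one arm, or by women who differ more from their arm in one group than in the other, the ITT and per-protocol estimates can move together. Their agreement would then be read as support that it does not provide. The trial exists to produce an effect size and confidence interval for deciding on a larger study, so a shift of a point or so on the ISI is relevant.

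**Working it through.** Positive differences below mean a larger ISI reduction in the add-on arm.

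**1. The plan's own figure.** Inputs from section 4.5: difference 4, SD 4.3, two-sided alpha 0.05, power 90%.

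- n = 2 × 4.3² × (1.960 + 1.282)² / 4² = 24.3, so 25 per arm by the normal formula.
- Power from the noncentral t distribution is 89.7% at 25 and 90.8% at 26, so 26 per arm.
- 26 / 0.85 = 30.6, so 31 per arm and 62 in total. The plan's figures reproduce.

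**2. Is imputation expected?** 10% of 62 is 6.2 women; 15% of 62 is 9.3. At the planned attrition the trigger is passed. If only 5 women were missing (5/62 = 8%), no imputation is stated, and ITT and per-protocol would both rest on much the same observed women.

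**3. Size of a possible bias.** Let p_A and p_C be the proportions lost in the add-on and control arms, and let δ be how many points worse the lost women are than those retained in the same arm. The bias towards the add-on is (p_A − p_C) × δ.

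- Equal loss and equal δ: 0.
- 15% against 0%, δ from 4 to 8: 0.6 to 1.2 points.
- 0% against 15%, same δ: the same size, against the add-on.

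**4. Tipping point.** Take 26 analysed per arm and 15% loss, and let only the add-on arm's lost women be worse than imputed.

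- SE = 4.3 × √(2/26) = 1.193; half-width of the 95% CI = 2.009 × 1.193 = 2.395.
- Each point of δ moves the difference by 0.15, so the CI reaches zero at δ = (observed difference − 2.395) / 0.15.

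| Observed difference | δ at which the CI reaches zero |
|---|---|
| 2.5 | 0.7 |
| 3.0 | 4.0 |
| 4.0 (planned) | 10.7 |

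This holds the CI width fixed, which is an approximation. With the SE on all 31 per arm (4.3 × √(2/31) = 1.092, half-width 1.96 × 1.092 = 2.14) and 5 of 31 add-on women lost, the values are (2.5 − 2.14) × 31/5 = 2.2 and (4.0 − 2.14) × 31/5 = 11.5.

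**5. Would the two planned analyses disagree?** A simulation with no true effect used 31 per arm, SD 4.3 and 1,000 runs. Imputation was missing-at-random on arm, baseline and Week 2 ISI. The correlations were assumed: baseline–Week 2 0.5, baseline–Week 4 0.4, Week 2–Week 4 0.6. An analysis of retained women stands in for per-protocol. Percentages are falsely significant results favouring the add-on (nominal 2.5%).

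| Lost, add-on vs control | Retained only | Imputed ITT |
|---|---|---|
| 9 vs 0, at random | −0.06 (2%) | −0.08 (2%) |
| 5 vs 4, worst Week 4 scores | 0.13 (3%) | 0.15 (3%) |
| 5 vs 0, worst Week 4 scores | 0.68 (7%) | 0.76 (8%) |
| 9 vs 0, worst Week 4 scores | 1.21 (16%) | 1.37 (19%) |
| 9 vs 0, worst changes | 2.25 (48%) | 1.29 (22%) |

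In every selective one-sided case both analyses erred in the same direction. With near-balanced loss there was almost nothing to detect. The 9 vs 0 rows are extremes, not forecasts.

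**The case against.** The strongest reply is that per-protocol beside ITT is the customary check on non-adherence, and that a fuller analysis plan, which section 8 says is available on request, may hold a proper missing-data sensitivity analysis. The absence of one from this article is therefore not itself the point. What stands is that section 4.10 gives the robustness role to the per-protocol analysis within its missing-data item, and that analysis cannot fill the role there.

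Several other replies hold and limit the point:

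- A reader might infer that women lost for worsening will create a spurious benefit of the add-on. The documents do not support that. Worsening alone is not automatic withdrawal, non-compliance does not by itself end participation, and section 3.6.3 gives both arms the same follow-up and safety oversight. On the plan's own expected means (10.9 control, 6.9 add-on), poor responders could as easily be lost from the control arm, which would bias against the add-on.
- The 30–40% early discontinuation quoted in section 1.1 concerns CBT-I in cited literature, not missing ISI in this trial. The plan's figure is 15%.
- Week 2 ISI is collected. An imputation model that uses it could absorb worsening that shows by then.
- The per-protocol population is not defined in the article. That it would select more strictly in the add-on arm follows only if the section 3.9 thresholds define it.
- The trial is exploratory and its p-values are descriptive. That lowers the stakes and favours reporting estimates over a significance threshold, but does not make per-protocol a test of the missing-data assumption.

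**Conclusion.** The point holds in a limited form. The analysis named for robustness does not vary the assumption about unseen Week 4 scores, and the withdrawal and retention rules make outcome-related loss possible. Whether bias arises, and in which direction, depends on loss being unequal between arms or differently related to outcome; the documents establish neither.

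At 15% loss in one arm only and δ of 4 to 8 points, the shift is 0.6 to 1.2 ISI points. An observed difference equal to the planned 4 points would withstand a large departure (10.7 points); one of 2.5 to 3 points would not withstand a modest one (0.7 to 4.0). The split of the loss, the values of δ and the score correlations are assumptions. This should be changed before the data are analysed, but it does not undermine the trial.

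**What to change.** Add to section 4.10 a delta-adjusted multiple imputation of Week 4 ISI as the missing-data sensitivity analysis. Impute within arm using baseline and Week 2 ISI. Then add, for example, 0, 2, 4, 6 and 8 points to the imputed scores in the add-on arm only, in the control arm only, and in both. Report the estimate and 95% CI at each value, in keeping with the plan's focus on estimation.

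Keep per-protocol as a supplementary analysis of adherence, and say that it is not the robustness check for missing data. If it uses the section 3.9 thresholds, apply one criterion common to both arms (at least six CBT-I sessions), because the oil threshold selects in the add-on arm only.

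The cost is a sentence or two and a few lines of R, with no new data. The downside is a little more analysis, and the result may look less robust.
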